## Abstract

**Background:**

A functioning vascular access (VA) is crucial to providing adequate hemodialysis (HD) and considered a critically important outcome by patients and healthcare professionals. A validated, patient-important outcome measure for VA function that can be easily measured in research and practice to harvest reliable and relevant evidence for informing patient-centered HD care is lacking. Vascular Access outcome measure for function: a vaLidation study In hemoDialysis (VALID) aims to assess the accuracy and feasibility of measuring a core outcome for VA function established by the international Standardized Outcomes in Nephrology (SONG) initiative.

**Methods:**

VALID is a prospective, multi-center, multinational validation study that will assess the accuracy and feasibility of measuring VA function, defined as the need for interventions to enable and maintain the use of a VA for HD.

The primary objective is to determine whether VA function can be measured accurately by clinical staff as part of routine clinical practice (Assessor 1) compared to the reference standard of documented VA procedures collected by a VA expert (Assessor 2) during a 6-month follow-up period. Secondary outcomes include feasibility and acceptability of measuring VA function and the time to, rate of, and type of VA interventions.

An estimated 612 participants will be recruited from approximately 10 dialysis units of different size, type (home-, in-center and satellite), governance (private versus public), and location (rural versus urban) across Australia, Canada, Europe, and Malaysia.

Validity will be measured by the sensitivity and specificity of the data acquisition process. The sensitivity corresponds to the proportion of correctly identified interventions by Assessor 1, among the interventions identified by Assessor 2 (reference standard). The feasibility of measuring VA function will be assessed by the average data collection time, data completeness, feasibility questionnaires and semi-structured interviews on key feasibility aspects with the assessors.

**Discussion:**

Accuracy, acceptability, and feasibility of measuring VA function as part of routine clinical practice are required to facilitate global implementation of this core outcome across all HD trials. Global use of a standardized, patient-centered outcome measure for VA function in HD research will enhance the consistency and relevance of trial evidence to guide patient-centered care.

**Trial registration:**

Clinicaltrials.gov: NCT03969225. Registered on 31st May 2019.

**Supplementary Information:**

The online version contains supplementary material available at 10.1186/s12882-022-02987-1.

## Background

Hemodialysis (HD) is the commonest treatment for patients with kidney failure worldwide and can only be provided via a functioning vascular access [1]. Establishing and maintaining a functioning access, however, is one of the greatest challenges in caring for these patients. Vascular access-related complications and interventions are associated with increased patient morbidity and mortality and healthcare costs accounting for 20–25% of annual hospital admissions in patients on HD [2–4]. From a patient’s perspective, the experience and anticipation of vascular access complications are key sources of stress and can lead to anxiety about the potential for vascular access failure [5]. Improving vascular access outcomes is therefore considered a critical priority not only by patients, but also their caregivers and health professionals [6–8].

Despite increasing numbers of vascular access trials, successful interventions to improve vascular access outcomes have been sparse and compromised by highly variable, often selectively reported outcomes of limited relevance to patients and health professionals [9, 10]. Based on a systematic review of vascular access outcomes in HD trials, vascular access function was the most frequently reported outcome, yet was described in 489 different ways with “mean access blood flow” and “number of thromboses” being the most frequently used measures. Despite efforts to standardize outcome definitions for vascular access by various working groups [11–14], only a minority of HD trials made use of these standardized definitions. For example, of the 134 patency measures reported across 64 trials, only 13% were consistent with 1 or more of the standardized definitions as proposed by national and international consortiums and societies [10]. These findings underpin the need for broader implementation of standardized, patient-important outcome measures to enhance the consistency and relevance of outcome reporting in clinical trials in HD. To address this issue, considerable efforts have been made to identify and standardize vascular access outcomes that are important to patients, their caregivers and healthcare professionals that should be reported consistently in clinical research to improve the quality, reliability and relevance of research evidence that guides patient care [15, 16]. The Standardized Outcomes in Nephrology in HD (SONG-HD) initiative identified vascular access as one of four critically important core outcome domains (along with fatigue, cardiovascular disease and mortality) for clinical trials in HD based on a consensus-based, multiphase, mixed-methods process involving over 1300 patients, caregivers and health professionals from more than 70 countries [6, 8, 17–19]. Based on international contributions of 237 patients and 720 clinicians, researchers, policy makers and industry from 58 different countries, “vascular access function” was deemed the most critically important outcome because of: 1. the broad applicability of function regardless of the vascular access type; 2. the involvement of a multidisciplinary team in achieving a functioning vascular access; and, 3. the impact of vascular access function on quality of life, survival, and other vascular access-related outcomes. “The need for interventions to enable and maintain the use of a vascular access for HD” was considered a simple, pragmatic, and inexpensive measure of vascular access function that was meaningful and relevant to patients [20]. Stakeholders considered the frequency (rate) of vascular access interventions and the intervention-free time to be key descriptors of a functioning vascular access [20]. In order to ensure global implementation of this outcome measure across all trials in HD, it needs to be feasible to accurately measure vascular access function as part of routine clinical practice without requiring additional resources or expertise in vascular access [20, 21].

While vascular access interventions have been reported in HD research and collected by renal registries [22–27] the granularity of data collection (i.e., type of vascular access interventions, date of intervention, and indication of intervention) vary substantially across studies and registries precluding reliable comparisons across trials and countries to inform research and clinical practice. A Canadian experience including five Canadian dialysis programs has shown that granular data collection of all types, dates, and indications of vascular access interventions in patients on HD using the Dialysis Measurement Analysis and Reporting (DMAR) system is feasible and reliable [22, 27, 28]. However, it remains unknown whether these data can be collected in other countries and different settings (i.e., in-center versus satellite versus home-based HD; rural versus urban; private versus public; small versus large units) by clinical staff without special expertise in vascular access and as part of routine clinical practice. VALID will address this uncertainty by assessing the validity, acceptability and feasibility of measuring vascular access function, defined by the need for interventions to enable and maintain the use of a vascular access for HD, by clinical staff as part of their routine clinical practice in a prospective, multi-center, multinational validation study covering a broad range of HD settings to ensure successful implementation of this core outcome measure in research and clinical practice without the need for additional resources or expertise in vascular access [21].

## Methods

### Aims

The primary aim of this study is to determine the accuracy of collecting vascular access interventions required to enable and maintain the use of a vascular access for HD by clinical staff as part of routine clinical practice compared to the reference standard of the documented vascular access procedures collated by a vascular access expert during a 6-month follow-up period.

Secondary aims are to assess the feasibility of this data collection process across different clinical settings and countries and to assess the accuracy of collecting details on all vascular access interventions including types of interventions.

We hypothesize that vascular access function can be measured accurately by clinical staff as part of routine clinical practice without requiring advanced vascular access and research expertise, significant time investment or costly equipment.

### Study design and setting

VALID is a prospective, multi-center, multinational validation study that will assess the accuracy and feasibility of measuring vascular access function in patients undergoing maintenance HD by clinical staff as part of routine clinical practice in 10 HD centers across 7 countries (Australia, Canada, France, Malaysia, the Netherlands, Switzerland, and the United Kingdom). The study schema is displayed in Fig. 1. Study sites have been purposefully selected to capture a broad range of different HD settings including geographical location (international sites, rural/remote and urban HD units), unit size (small to large HD units), HD modality (in-center-, satellite, home-based HD) and setting (private versus public hospital).

**Fig. 1 Fig1:**
[figure not shown]
Study Schema. Abbreviations: HD – Hemodialysis; VA – Vascular Access. The study design aligns with the STARD 2015 guidelines: An Updated List of Essential Items for Reporting Diagnostic Accuracy Studies [29]

The study will be conducted according to International Council for Harmonization of Technical Requirements for Pharmaceuticals for Human Use (ICH) Good Clinical Practice (GCP) guidelines and will be reported according to the Standards for Reporting of Diagnostic Accuracy (STARD) guidelines [29]. The study will be conducted and coordinated by the Australasian Kidney Trials Network (AKTN), led by an International Trial Steering Committee of vascular access experts including two patient partners, study investigators, statisticians, and other researchers (Fig. 2). The VALID study protocol was registered with the ClinicalTrials.gov (NCT03969225) on 31st May 2019. Ethics Approval has been granted for all participating sites (please refer to the Declaration Section for further details). Written consent will be obtained from study participants by the site investigators in line with the site-specific ethics approval document.

**Fig. 2 Fig2:**
[figure not shown]
Study Governance Structure. Abbreviations: AKTN – Australasian Kidney Trials Network; UQ – University of Queensland, Australia

### Study participants

All patients receiving maintenance HD in the participating units and who are able and willing to provide informed consent (unless a waiver of consent is approved by the local ethics committee), will be invited to take part in the trial. Patients who are expected to require HD for less than 3 months due to anticipated recovery of kidney function or are considered unsuitable to participate by clinical staff will be excluded. The eligibility criteria are deliberately kept broad to reflect routine clinical practice (i.e. not excluding non-English speaking patients) and avoid selection bias within participating units. Pediatric patients are excluded because vascular access outcomes were not considered a core outcome domain for research in pediatric patients with chronic kidney disease, as established by the SONG-Kids initiative [30].

### Test method

#### Index test

A clinical staff member (Assessor 1) of the participating HD center without special expertise in vascular access research will collect the number, type and date of any vascular access interventions required to enable and maintain the use of the participants’ vascular accesses for HD. Data will be entered in the Research Electronic Data Capture (REDCap), a secure, web-based data base application designed to support data capture for research studies and hosted by the Queensland Clinical Trials and Biostatistics Centre at the University of Queensland [31]. Assessor 1 will be, in most cases, a HD nurse working in the HD unit. Alternatively, Assessor 1 may also be a HD technician, a medical or nursing student or a junior doctor. Data collection for each patient will occur for 6 months or until the patient’s death, transfer to a different kidney replacement therapy (i.e., peritoneal dialysis, kidney transplantation), treatment withdrawal, transfer to a different unit, or kidney recovery with removal of any HD vascular access. Information on vascular access interventions will be acquired as per local practice. Resources may include (but are not limited to) electronic or paper-based medical records, existing databases, or information provided by staff or patients. Assessor 1 may prospectively enter the details on vascular access interventions into REDCap as they occur or retrospectively at 3 and 6 months of follow-up.

#### Reference standard

The reference standard represents the vascular access procedure notes (i.e., source document) collected by a vascular access expert of the research team, henceforward referred as Assessor 2. The redacted procedure notes will be uploaded into REDCap. Assessor 2 will collect the data independently from Assessor 1. Moreover, Assessor 2 will not be able to access data on vascular access interventions entered by Assessor 1 and vice versa. Assessor 2 may collect these data prospectively or retrospectively at 3 and 6 months of follow-up. This reference standard reflects the accepted research standard of collecting data on vascular access events (i.e., interventions).

#### Audit assessor role

To ensure completeness and accuracy of data collection by Assessor 2 as the gold standard, a local audit assessor at each site (typically the site principal investigator) will check completeness and verify vascular access procedure notes of 10% of randomly selected participants. In case of VA intervention missingness or inaccuracy for more than 1 participant, the audit assessor will cross-check data accuracy and completeness for all remaining study participants enrolled at the unit.

#### Maintenance of independence of assessors

In view of the importance of independence of Assessor 1 (Index test) and Assessor 2 (Reference standard), the database structure has been designed to engage role-based access control for assessors. This ensures that assessors of one category (Assessor 1, Assessor 2 or Audit Assessor) can only access the relevant sections in the database for their role, enabling them to only perform functions specified by the study protocol for that role.

### Data collection

#### Participant demographic and medical history

Table 1 summarizes the data collection timepoints for Assessor 1 and 2, respectively. Baseline data will be collected by the site investigators, typically Assessor 2, including patient demographics (sex, age, ethnicity), comorbidities (diabetes mellitus, cardiovascular diseases [ischemic heart disease, cerebrovascular accidents, peripheral vascular disease], BMI), HD and vascular access details (HD setting [in center, satellite, home HD, in center nocturnal HD, home nocturnal HD], dialysis duration, usual number of dialysis sessions per week, usual number of hours of dialysis per week, vascular access in use, location of AVF/AVG in use [upper arm, lower arm or leg], self-cannulation and cannulation technique [Rope ladder versus button hole]).

**Table 1 Tab1:** Data collection schedule

Time point of data collection (months)	Assessor 1 (Index test)			Assessor 2 (Reference standard)		
	0	3	6	0	3	6
Assessor characteristics	√			√		
Patient consent (if required)				√		
Patient characteristics				√		
Number of vascular access intervention(s)		√	√		√	√
Type of vascular access intervention(s)		√	√		√	√
Date of vascular access intervention(s)		√	√		√	√
Extraction of procedure notes					√	√
Indication for vascular access intervention					√	√
Time required to collect/enter vascular access intervention data		√	√		√	√
Study end / Early exit		√^a^	√		√^a^	√
Feasibility questionnaire			√			√
Semi-structured interview			√			√

^a^Early exit from the study

Information about the roles and expertise of Assessors 1 (index test) and Assessors 2 (reference standard) will also be collected at baseline including role/profession, and years of experience in HD, in clinical research and in vascular access monitoring/maintenance.

#### Vascular access interventions

Table 2 lists all vascular access interventions considered for defining vascular access function and encompasses any interventions/procedures required to enable and maintain the use of the vascular access for HD during the study period. The selection of vascular access interventions was informed by previous research [22, 27, 28] and feedback from patients, caregivers and health professionals with expertise in vascular access [20, 32]. Interventions are considered relevant if they are performed to enable and maintain the function of the vascular access and are regarded as invasive or disruptive to the patient, i.e., potentially painful and requiring a visit to the operating room, radiology suite or special procedure room or are conducted by the bedside. To facilitate data accuracy verification, Assessor 2 will also collect the indication for each of the vascular access interventions (Supplementary Item S1).

**Table 2 Tab2:** Vascular access interventions required to enable or maintain the use of a vascular access for hemodialysis

Vascular access	Intervention/Procedure
**AVF/AVG**	Open surgical or endovascular creation/placement of AVF/AVG
	Open surgical revision or endovascular intervention of AVG/AVF
	Thrombolysis or thrombectomy of AVG/AVF
	Ligation or resection of arteriovenous access
	Repair of aneurysm/pseudoaneurysm
	Competing/collateral vein ligation
	Fistulogram (Angiogram) +/− angioplasty +/− stenting (including inflow artery, body of AVF/AVG, venous outflow, central vein)
	Competing/collateral vein embolization
	Superficialization/transposition
	Management of Dialysis Associated Steal Syndrome (DASS)/Access Induced Ischemia. Procedures include:
	• Distal Revascularisation, Interval Ligation (DRIL)
	• Proximalization of the Arterial Inflow (PAI)
	• Revision Using Distal Inflow (RUDI)
	• Banding
**CVC**	CVC insertion
	CVC exchange
	Fibrin sheath removal/disruption
	CVC removal

Vascular access interventions not to be included: Repositioning of patient on HD chair/bed, reversing of CVC lines, flushes of CVC lines, repositioning of dialysis needles in AVG or AVF, thrombolytics for CVC lines, use of antibiotics for vascular access-related infections

*Abbreviations*: *AVF* Arteriovenous fistula, *AVG* Arteriovenous graft, *CVC* Central venous catheters (tunnelled and un-tunnelled)

#### Feasibility assessment

Both data collectors, Assessors 1 and 2, will be prompted to complete a feasibility questionnaire addressing all relevant feasibility aspects, as outlined by Prinsen et al. [33] at the end of study (Supplementary Item S2).

#### Semi-structured interview

At study end, face-to-face or video-call semi-structured interviews will be performed with all Assessors. The interview question guide is outlined in Supplementary Item 3. All interviews to be conducted in English will be performed by the Chief Principal Investigator AV and expected to take approximately 30 minutes. If required, interviews will be conducted in the assessor’s native language by a bilingual member of the SONG vascular access working group [32]. The interview serves to further explore assessors’ perspectives on the feasibility of measuring vascular access function. The interviews will be audio-recorded and transcribed verbatim.

#### Early withdrawal from the study

Once a participant has been included in the study, the investigator will make every reasonable effort to keep the participant in the study. Reasons that participants may be withdrawn from the study prior to study end include death, kidney transplantation, transfer to peritoneal dialysis, permanent withdrawal from kidney replacement therapy, transfer to another HD unit which is not an active study site, loss to follow-up, withdrawal of participant consent and at the discretion of the treating physician. In case of early termination of participation, the Site Principal Investigator or co-investigator (assessors 1 or 2) will complete the study end form at time of withdrawal of the participant.

### Study outcome measures

#### Primary outcome measures

The primary outcome will be the accuracy of reporting vascular access function during a 6-months period, defined by the need for any intervention(s) required to enable and maintain the use of a vascular access for HD. The accuracy of reporting vascular access function is defined by the correct identification of each intervention and the correct reporting of the total number of interventions per patient. An intervention reported by Assessor 1 will be considered correctly identified if its intervention date is within +/− 3 days of the date identified by Assessor 2 (the reference standard).

#### Secondary outcome measures

Accuracy of the reported type of VA intervention will be analyzed as secondary outcomes. Clinical outcomes include the rate of vascular access interventions (n/patient-year), the time to first vascular access intervention, and the type of vascular access interventions. Feasibility outcome measures include the time required for measuring vascular access function, completeness of data collection, Likert score of feasibility questionnaire with data collectors (Assessors 1 and 2), qualitative analysis of semi-structured interview with data collectors, and study feasibility outcomes including recruitment rate, eligibility ratio and enrolment ratio.

#### Adverse events

The study has no impact on patients’ safety, or the care provided to participants during the study conduct. No adverse events (serious or not) will be collected for this study other than the outcome measure of interest and outcomes captured as reasons for early termination of participant follow-up due to outcomes such as death or treatment withdrawal.

### Statistical considerations

#### Sample size calculation

The sample size has been calculated for the sensitivity, i.e. the proportion of interventions correctly identified by Assessor 1 and specificity, i.e. the proportion of patients with no interventions recorded by Assessor 1 that do not have a record of interventions.

Assuming an event rate of 2 vascular access interventions/ patient-year based on recent data from a study collecting a comparable range of vascular access interventions in HD patients [28], the overall expected number of interventions over a 6 month period will be equal to the number of participants, although there will be patients with no intervention and patients with more than one intervention. Assuming a true sensitivity of 90%, 520 records of interventions will provide an approximate 5% width for the 95% confidence interval.

With the rate of 2 vascular access interventions/ patient-year and assuming a Poisson distribution, the expected number of patients without an intervention in the 6 months is 193. This number will allow the calculation of the specificity with a 10% width for the 95% confidence interval, assuming a true specificity of 90%.

The sample size will be inflated to account for 15% potential dropouts (i.e. early study exit). This corresponds to a final sample size of 612 patients.

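### The 10% interval width stated for specificity does not follow from 193 patients at 90%: under independence the width is about 8.5 to 9 points (minor correction)

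*Protocol article*

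**What the plan says.** All the inputs are in the protocol article, Statistical considerations, Sample size calculation. The section sizes the study on two measures, sensitivity and specificity.

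- **Event rate and count.** The section starts from "Assuming an event rate of 2 vascular access interventions/ patient-year", so that "the overall expected number of interventions over a 6 month period will be equal to the number of participants".
- **Sensitivity.** "Assuming a true sensitivity of 90"%, it says that "520 records of interventions will provide an approximate 5% width for the 95% confidence interval".
- **Specificity.** It then says that, "assuming a Poisson distribution, the expected number of patients without an intervention in the 6 months is 193", and that this number allows estimation of "specificity with a 10% width for the 95% confidence interval", "assuming a true specificity of 90"%.
- **Inflation.** A 15% allowance for early exit brings the total to 612.

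The section names no interval method for planning and states no design effect. The Accuracy and validity assessment section plans confidence intervals for both measures from logistic GEE models with robust standard errors. Clustering by center and by patient is handled in separate models.

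**The concern.** The two widths stand in consecutive paragraphs, use the same assumed true value (90%) and the same confidence level, and differ only in the denominator. One would expect a single formula to give both. It gives the first and not the second.

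What is at stake is limited. Specificity is one of the two measures on which the study is said to be sized, and a reader should be able to reproduce its stated precision. A figure that matches no standard interval leaves the reader unsure whether it is loosely rounded, rests on an unstated allowance, or is a slip.

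**Working it through.** **Inputs (Sample size calculation section).** Rate 2 per patient-year; follow-up 0.5 year, so a Poisson mean of 1 per patient; 520 records, equated with 520 participants; 193 patients expected without an intervention; true sensitivity and specificity both 90%; 95% confidence; 15% early exit.

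**Formula.** The full width of a Wald interval is 2 × 1.96 × √(p(1 − p)/n).

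**Step 1: reproduce the figures that do follow.**
- Sensitivity: 2 × 1.96 × √(0.09/520) = 0.0516, or 5.16 points. Other standard intervals give up to 5.36. This agrees with approximately 5%, and shows that width means full width under independence.
- Inflation: 520/0.85 = 611.8, which gives 612.

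**Step 2: apply the same formula to specificity.** 2 × 1.96 × √(0.09/193) = 0.0846, or about 8.5 points.

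**Step 3: try other interval methods at n = 193.**

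| Method | Full width (points) |
|---|---|
| Wald | 8.47 |
| Wilson | 8.53 |
| Logit | 8.61 |
| Agresti-Coull | 8.67 |
| Exact (Clopper-Pearson) | 8.9 to 9.0 |
| Wald, continuity-corrected | 8.98 |
| Wilson, continuity-corrected | 9.03 |

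None gives 10.

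**Step 4: invert.** A 10-point Wald width needs n = 4 × 1.96² × 0.09/0.10² = 138.3, so 139 patients. Wilson needs 141, exact 158 and continuity-corrected Wilson 160. All are well below 193.

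**Step 5: other readings of the 10%.**
- As a half-width it fits worse: the Wald half-width at 193 is 8.47/2 = 4.2 points.
- Taking the 15% loss off the 193 leaves 193 × 0.85 = 164 patients, with widths of 9.2 (Wald) to 9.9 points (continuity-corrected Wilson). That comes near 10, but the section ties the width to 193 and deals with early exit afterwards by inflating the total.

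**Step 6: the expected count.** 520 × exp(−1) = 191.3, against 193. The gap is 1.7 patients, or 0.9%. Using 0.37 for exp(−1) gives 192.4, so rounding is a likely source. The Wald width at 191 is 8.51 points, a change of 0.04.

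**The case against.** The strongest defence is that the figure errs on the safe side. Under independence, 193 patients deliver a 10-point width with some to spare, so the sentence can be read as a coarse target that is met. The number also drives nothing: 520 and 612 follow from the sensitivity target and the early-exit inflation alone, and the Trial status section reports that recruitment closed in November 2021. This stands, and it is why the point is minor. It does not make the figure right. The sentence does not say at most or approximately, and the neighbouring sensitivity figure is close to its calculated value.

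A second defence is that 10% may be nearer to what the planned clustered analysis will give than 8.5% is. This is fair as far as it goes: GEE intervals allowing for clustering may well be wider than the independence value. The corrected text should say so, and should not present 8.5% as the precision to expect from the final analysis.

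Two stronger readings are tempting, and the document supports neither.

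- **A hidden clustering allowance.** A reader might infer that the gap is a deliberate allowance. It would correspond to a variance inflation of (10/8.465)² = 1.40, but that value is obtained only by working back from the gap. The section states no design effect or intracluster correlation, and the sensitivity width reproduces with no inflation. Loose rounding explains the text equally well.
- **A wrong expected count.** A reader might infer that 193 is a second error. The difference is of rounding size and has no practical effect on the width.

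**Conclusion.** The stated specificity width is wrong as written. On the basis on which the sensitivity width reproduces, 193 patients at 90% give about 8.5 points (Wald or Wilson) to about 9 points (exact or continuity-corrected). The stated 10 is therefore too wide by about 1 to 1.5 points. The value 8.5 holds only for Wald-type intervals; because the section names no method, the range is the safer statement.

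The conclusion assumes independent patients, a full two-sided 95% width and a denominator of 193, as the section itself gives. Under those assumptions the misstatement is conservative. It does not affect the sample size and is not evidence of a design fault. How far clustering will widen the final intervals cannot be worked out from the document and is not part of this finding.

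**What to change.** In the Sample size calculation section, replace the 10% by about 8.5% (Wald) or about 9% (exact) and name the interval method. Add one sentence saying that the figure assumes independence and that the planned GEE intervals, which allow for clustering, may be wider.

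If 10% was meant to include clustering, keep it, state the design effect used, and restate the sensitivity width with clustering allowed for on the same basis.

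In the same edit, tidy the expected count to about 191, or say how 193 was obtained.

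The cost is two figures and about one sentence. Nothing changes in enrolment, data collection or analysis.
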